## Abstract

Hypoxia activates hypoxia-inducible factors (HIFs), which regulate genes involved in erythropoiesis, angiogenesis, and metabolism. HIF stability is controlled by oxygen-dependent HIF prolyl 4-hydroxylases (HIF-P4Hs). Pharmacological HIF-P4H inhibitors are approved for the treatment of anaemia in chronic kidney disease (CKD). Beyond erythropoiesis, these drugs have been linked to improved lipid profiles in CKD, and preclinical studies suggest benefits for glucose tolerance and cardiovascular protection. However, cardiometabolic effects of HIF-P4H inhibitors have not been systematically examined in healthy or non-anaemic individuals. This investigator-initiated, double-blind, placebo-controlled, randomised crossover trial evaluates the systemic effects of roxadustat, an orally administered pan-HIF-P4H inhibitor. The study consists of two 10-day study arms separated by a minimum 4-week washout. Participants receive 70 mg of roxadustat or a placebo thrice a week. The primary hypothesis is that roxadustat lowers plasma total cholesterol. Secondary outcomes include changes in LDL cholesterol, triglycerides, insulin sensitivity, glucose tolerance, body composition, 24 h blood pressure, exercise capacity, autonomic cardiovascular regulation, and skeletal muscle microcirculation. Healthy volunteers (*n* = 24) aged 18–40 years will be enrolled. This study will provide insights into the potential of HIF-P4H inhibitors for obesity, dyslipidaemia, insulin resistance, and hypertension, and may inform future therapeutic strategies for metabolic syndrome, type 2 diabetes, and cardiovascular disease.

## 1. Introduction

A decrease in oxygen concentration leads to hypoxia, which activates a physiological response mechanism. Hypoxia-inducible factor (HIF) is the central transcription factor in this response [1]. Through its target genes, HIF regulates numerous biological pathways, including erythropoiesis and iron metabolism, angiogenesis, energy metabolism, and inflammatory responses [1]. HIF is regulated by three oxygen-dependent HIF prolyl 4-hydroxylase enzymes (HIF-P4Hs 1-3) [1]. The HIF response can be pharmacologically activated by small-molecule HIF-P4H inhibitors [1,2]. The first clinical HIF-P4H inhibitor, roxadustat (Evrenzo), was approved by the European Medicines Agency in August 2021 for the treatment of severe anaemia caused by chronic kidney disease (CKD). To date, clinical trials investigating roxadustat have primarily involved anaemic CKD patients, focusing on its erythropoietic effects and safety [3,4,5,6,7,8,9,10]. Roxadustat is used in both dialysis-dependent (CKD-D) and non-dialysis-dependent (CKD-ND) patients. In addition to its erythropoietic properties, HIF-P4H inhibitors have shown favourable metabolic effects on blood lipid profiles in CKD and peritoneal dialysis patients, lowering total cholesterol, low-density lipoprotein (LDL) cholesterol and triglyceride levels; an effect differentiating them from classical erythropoiesis-stimulating agents, like erythropoietin (EPO) [3,4,10]. Roxadustat and other HIF stabilisers are classified as prohibited substances by the World Anti-Doping Agency (WADA) under category S2: peptide hormones, growth factors, related substances, and mimetics [11].

Beyond CKD patients, HIF-P4H inhibitors have improved blood lipid profiles in animal models. They also reduce adipose tissue mass and inflammation, improve glucose tolerance, and decrease insulin resistance and liver fat accumulation [12,13]. In preclinical studies, pharmacological HIF-P4H inhibition and genetic silencing of *HIF-P4H-2*, the most abundant isoenzyme, have shown benefits in myocardial ischemia and atherosclerosis [14,15,16,17,18]. Roxadustat has also been reported to lower systolic blood pressure in preclinical models [18,19]. HIF target genes such as *NOS3*, *TIE2*, and *APJ* regulate small vessel calibre, and silencing of *HIF-P4H-2* has been shown to enlarge cardiac and skeletal muscle capillaries [15,20]. *MCT4*, which regulates lactate export, is also a HIF target gene, and its upregulation via *HIF-P4H-2* silencing in mice enhances lactate clearance and reuse, protecting against lactic acidosis [20,21].

Despite active research in cell and animal models, the effects of HIF-P4H inhibitors outside their primary erythropoietic indication, particularly in cardiometabolic diseases or among healthy study populations, have not been investigated in clinical trials. Therefore, this study will generate new insights into the potential of HIF-P4H inhibition to influence key metabolic and cardiovascular parameters. These findings may be relevant to the development, prevention, and treatment of obesity, dyslipidaemia, insulin resistance, atherosclerosis, and hypertension. In the future, HIF-P4H inhibitors may potentially become part of the pharmacological treatment for metabolic syndrome, type 2 diabetes, and cardiovascular diseases.

The aim of this study is to investigate the effects of the HIF-P4H inhibitor roxadustat on metabolism and cardiovascular function in healthy volunteers. The primary hypothesis of the study is that roxadustat lowers plasma total cholesterol levels. The secondary hypotheses are that roxadustat lowers plasma LDL cholesterol and triglyceride levels, reduces insulin resistance and improves glucose tolerance in a 2 h oral glucose tolerance test (OGTT), lowers 24 h blood pressure, improves exercise tolerance and autonomic regulation of cardiovascular function, enhances skeletal muscle microcirculation and has a favourable effect on body composition.

## 2. Experimental Design

### 2.1. Trial Design

The study is double-blind, placebo-controlled, and crossover in design. It consists of two 10-day study arms separated by a washout period of at least 4 weeks. The study plan involves recruiting 24 healthy volunteers and administering 70 mg of roxadustat orally (Evrenzo 70 mg, Astellas Pharma (Tokio, Japan), encapsulated in a white capsule) thrice a week over a 10-day period (a total of 4 doses). The effects will be compared to a matched placebo arm, during which participants will receive white placebo capsules thrice a week. Participants are randomised to a treatment sequence. Half of the participants will be randomised to receive roxadustat during study arm 1 and placebo during arm 2, while the other half will receive placebo in arm 1 and roxadustat in arm 2. The randomization will be conducted by the hospital pharmacy of Oulu University Hospital, which holds the randomization code. The code will be unblinded at the end of the study, at which point the pharmacy will provide the allocation information to the principal investigator. At the end of each study arm, participants will undergo blood sampling, a 2 h OGTT, 24 h ambulatory blood pressure monitoring, anthropometric and body composition measurements, heart rate variability assessment, skeletal muscle microcirculation measurement, and a maximal exercise test.

The study will be conducted at the Research Unit of Internal Medicine in the Oulu University Hospital, Oulu, Finland, the Physiology Research Laboratory in the Research Unit of Biomedicine and Internal Medicine, Faculty of Medicine, University of Oulu, and the Faculty of Biochemistry and Molecular Medicine, University of Oulu.

### 2.2. Participants

#### 2.2.1. Inclusion and Exclusion Criteria

Inclusion criteria are healthy volunteers (both women and men, no gender ratio has been stipulated) aged 18–40 years confirmed by medical history, a clinical examination conducted by a physician, and safety laboratory tests (Complete blood count (CBC), plasma potassium, sodium, creatinine, ALT, AFOS, bilirubin, TSH, glucose, hCG (women) from a fasted sample, and urine chemical screening) including an electrocardiogram (ECG)). Eligible participants must have a body mass index (BMI) over 20 kg/m^2^ and weigh less than 100 kg, which is the upper limit defined by the pharmaceutical company (Astellas Pharma) for administering 70 mg of Evrenzo (roxadustat) three times per week.

Exclusion criteria include regular medication use (including continuous allergy medication, thyroxine, and asthma medication, but excluding hormonal intrauterine devices), significant illnesses as assessed by the study physician, systolic blood pressure over 150 mmHg, haemoglobin (Hb) levels outside the Finnish reference ranges (134–167 g/L for men and 117–155 g/L for women), pregnancy and breastfeeding, needle phobia or history of difficult blood sampling, lack of Finnish language proficiency, substance or alcohol abuse, drug use, participation in another clinical trial within one month prior to study start, major surgery within six months prior to study start, allergy to peanuts or soy (the drug coating contains soy), history of venous thrombosis or seizures, significant familial predisposition to thrombosis, hereditary galactose intolerance, complete lactase deficiency, or glucose-galactose malabsorption. Women of childbearing age who are not sterilised or do not use an intrauterine device (IUD) or hormonal IUD during and for one week after the study periods are also excluded. The study is conducted by research nurses and physicians experienced in performing clinical trials and clinical drug studies, and are well-versed in the principles and practices of Good Clinical Practice (GCP). The study is monitored by a clinical trial monitor external to the research groups involved.

#### 2.2.2. Criteria for Discounting Interventions

Criteria for discontinuing an individual participant from the study include withdrawal of informed consent by the participant, any medical condition that, in the opinion of the principal investigator, may compromise the participant’s safety if study medication is continued, pregnancy, ineligibility for the study (either arising during the study or retrospectively identified and missed during screening), an adverse event requiring discontinuation of the study medication, significant non-compliance with the study or study procedures (e.g., dosing, study visits), loss to follow-up despite at least three documented attempts to contact the participant.

Study physicians, researchers and study nurses involved in the study inform the principal investigator of any interim findings that may warrant termination of the trial. The principal investigator makes the final decision regarding discontinuation of the study.

#### 2.2.3. Relevant Concomitant Care Permitted or Prohibited During the Trial

During the study arms and for one week following their completion, women of childbearing potential who are not sterilised must use an effective method of contraception (IUD or hormonal IUD). The use of herbal supplements, trace elements, vitamins, licoricey and salty licoricey (salmiakki) products, and energy drinks is prohibited during the study arms. Consumption of coffee and nicotine products/tobacco should be kept as consistent as possible across both study arms. Participants are asked to avoid significant deviations in fat quantity or quality from their usual diet, as well as highly salty foods; otherwise, a normal diet is recommended. Alcohol consumption is prohibited during the study arms. Participants are also asked to refrain from unusually strenuous physical activity during the study arms. Use of anti-inflammatory pain medications is discouraged during the study arms. For occasional pain, paracetamol is recommended. If the need for medication arises during the study, participants are asked to inform the study staff so that the safety of continued participation can be assessed. During the washout period, participants may follow their normal lifestyle.

#### 2.2.4. Sample Size

A total of 24 healthy volunteers will be recruited for the study. If any participants discontinue, new individuals will be recruited to ensure the final sample size remains at 24. The hospital pharmacy will assign the same treatment sequence to the replacement participant as was assigned to the one who withdrew. Data collected from participants who discontinue will not be used. With this sample size, the study has a 95% probability (power) of detecting a 0.3-unit (mmol/L) change in plasma total cholesterol levels at a two-sided significance level of 0.05, assuming a standard deviation (SD) of 0.38 mmol/L for the change in the primary outcome. The assumptions for this power calculation are based on a previous clinical trial evaluating the efficacy of roxadustat, in which a 3-wk treatment reduced plasma total cholesterol by 0.9 mmol/L more in CKD-ND patients (*n* = 82–84) compared to those treated with placebo (*n* = 43), with the between-group difference remaining consistent for up to nine weeks after treatment initiation [3].

#### 2.2.5. Compensations

Each participant will receive a one-time compensation of 120 €, in accordance with Regulation 82/2011, as reimbursement for participating in a medical trial that does not provide direct health benefits to the individual. Participants who complete only the first study arm will receive half of the total compensation. In addition, participants will gain valuable information about their blood values, body composition, blood pressure, circulation, autonomic nervous system function, and aerobic fitness.

If a personal injury occurs due to the investigational drug or procedure performed as part of the study, compensation may be sought. Compensation for harm caused by the investigational drug is applied for through the Pharmaceutical Injury Insurance. This insurance covers unexpected adverse effects caused by the investigational drug under conditions specified in the insurance terms. For personal injuries not caused by the investigational drug, compensation is sought through the patient’s insurance or the subject insurance of Oulu University Hospital or the University of Oulu.

#### 2.2.6. Plans to Ensure Complete Follow-Up

All participants will gain valuable information about their blood values, body composition, blood pressure, circulation, autonomic nervous system function, and aerobic fitness. Sharing these data with the participants is utilised to promote retention and ensure completion of the two study arms. Data collected from participants who discontinue will not be used in analyses.

### 2.3. Blinding and Randomization

The study is double-blind. Trial participants, care providers and outcome assessors will be blinded during the data collection. Randomization will be performed for the treatment sequence, and it is managed by the hospital pharmacy at Oulu University Hospital, which holds the randomization code. Half of the participants will be randomised to receive roxadustat during study arm 1 and placebo during arm 2, while the other half will receive placebo during arm 1 and roxadustat during arm 2. The pharmacy delivers the drugs in envelopes having the participant number (1–24) and study arm (1 or 2) to the research centre, where they are kept at room temperature in a locked cabinet. Any unused drugs are returned to the pharmacy, which is responsible for disposal. Both the study medicine (Roxadustat, Evrenzo 70 mg) and the placebo are packed in similar, white-coloured capsules. The code will be blinded until the end of the study (i.e., until 24 participants have completed two study arms), at which point the pharmacy will provide the allocation information to the principal investigator. In case of serious adverse events or pregnancy, the randomization code will be unblinded immediately.

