Study Day 9 (Morning, participant fasted for 10–12 h):Weight, waist and hip circumference are measured on Study Day 1.Blood pressure and pulse are measured on Study Day 1.Fasting blood samples are collected for the following analyses in the clinical laboratory (NordLab) of the Oulu University Hospital, and results are shared with participants: CBC with Differential, E-Reticulocytes, plasma Potassium, Sodium, Creatinine, ALT, AST, Bilirubin, ALP, gamma-GT, Albumin, TSH, Total Cholesterol, LDL, HDL, Triglycerides, hsCRP, HbA1c, lp(a). Additional analyses may be performed in academic or commercial labs.Additional blood samples (2 × 8 mL) are collected in CPT tubes (BD Biosciences, San Jose, CA, USA) for isolation of mononuclear cells and RNA extraction (RNeasy Mini Kit, Qiagen, Hilden, Germany) to study gene expression related to HIF response and drug metabolism. DNA is also extracted from the blood sample, enabling the potential to investigate genes that could be involved in glucose, lipid, hormone, bone, and drug metabolism, or blood pressure regulation.Serum and plasma samples (10 mL each; plasma with EDTA) are stored for potential additional analyses related to metabolism, including serum metabolomics and plasma 4β-hydroxycholesterol levels. If the participant withdraws, these samples will be destroyed.After blood sampling, a 2 h OGTT is performed. The participant drinks a solution containing 75 g of glucose. Venous blood samples are taken at 0, 30, 60, and 120 min to measure glucose, insulin, and C-peptide in Nordlab. These results are shared with the participants. At each time point, 2 × 5 mL blood samples are collected, immediately treated with a dipeptidyl peptidase IV (DPP) inhibitor, and used for glucagon, GLP-1 and GIP assays by ELISA at the Faculty of Biochemistry and Molecular Medicine, University of Oulu. One sample is stored for potential further analyses.Participants are instructed in the use of an ambulatory blood pressure monitor (Mobil-O-Graph, IEM GmbH, Aachen, Germany), which is worn for 24 h at home. Data is analysed using HMS-CS Hypertension Management Software, version 6.3 (IEM) [22].

Study Day 10 (Afternoon):
Participant returns the ambulatory blood pressure monitor.Body composition measurements:

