### 4.2. Statistical Analyses

Statistical analyses will be mostly conducted using Student’s paired (dependent samples) *t*-test, as each participant serves as their own control in a crossover study design, and the long interval between study arms is assumed to eliminate any sequence effect. The normality of the measured variables will be assessed. If a variable is not normally distributed, a logarithmic transformation will be applied prior to statistical analysis, or non-parametric tests will be used. For multivariable analyses, regression models will be employed as the statistical method. Principal component analysis will be used to account for multiple testing when necessary. Sensitivity analyses on potential period or carry-over effects will be conducted.

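### The randomisation code is released when the 24th participant finishes, with no requirement that signal-derived secondary outcomes, late exclusions and database lock come first

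*Protocol article*

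**What the plan says.** Section 2.3 (Blinding and Randomization) defines when the code may be opened: "The code will be blinded until the end of the study (i.e., until 24 participants have completed two study arms". The same sentence names the principal investigator as the person who then receives it from the pharmacy. Section 2.1 (Trial Design) gives the same rule: "The code will be unblinded at the end of the study". Section 2.3 states the scope of blinding as follows: "Trial participants, care providers and outcome assessors will be blinded during the data collection".

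Section 3.3 describes work that may continue after a visit. Some incretin-related samples are "used for glucagon, GLP-1 and GIP assays by ELISA at the Faculty of Biochemistry and Molecular Medicine, University of Oulu", and other serum and plasma samples "are stored for potential additional analyses related to metabolism, including serum metabolomics and plasma 4β-hydroxycholesterol levels". No date relative to unblinding is given for either. The same section has heart rate variability, NIRS and the maximal exercise test recorded on study day 10, when the ambulatory blood pressure monitor is also returned.

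Section 2.4 places the monitor's close-out visit after the final study visit. Section 2.2.2 lists ineligibility discovered in retrospect and significant non-compliance as grounds for discontinuing a participant. Sections 2.2.4 and 2.2.6 say that data from participants who discontinue are not used.

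**The concern.** In a double-blind trial the code is normally kept closed until the data are final. Here the release event is the last participant's completion of the second arm. Anything that still needs human judgement after that moment has no stated protection.

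Two kinds of decision are at stake. The first is turning recordings into outcome values. Autonomic regulation, skeletal muscle microcirculation, exercise tolerance and 24 h blood pressure are all named secondary outcomes in Section 4.1, and all rest on recordings that someone must reduce to numbers. The second is who counts in the analysis. A finding of ineligibility or poor compliance removes a participant's data, and such findings can surface at the end, when packages are counted and the monitor closes out. With 24 participants, one removal is 1/24 = 4.2% of the sample and takes one participant from a sequence of 12. If those decisions are made by someone who knows the allocation, the double-blind description does not cover them.

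**Working it through.** **1. The plan's own figure.** Section 2.2.4 gives n = 24, a difference of 0.3 mmol/L, an SD of the change of 0.38 mmol/L and two-sided alpha 0.05, with 95% power stated. For a paired t-test the noncentrality is 0.3/0.38 × √24 = 0.789 × 4.899 = 3.87 on 23 degrees of freedom, which gives 95.9% power. The stated figure reproduces, and the time of unblinding does not change it.

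**2. Order of events at the end of the trial.**

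| Step | Where stated | Position relative to the trigger |
|---|---|---|
| Trigger: 24th participant completes arm 2 | Sections 2.1, 2.3 | – |
| Last day-10 heart rate variability, NIRS and exercise recordings | Section 3.3 | Made at the visit that fires it |
| Last ambulatory monitor returned | Section 3.3 | Same visit |
| Last empty medication packages returned | Section 3.3 | Final visit of the arm, hence the same visit |
| Close-out monitoring visit | Section 2.4 | After the final study visit |
| Glucagon, GLP-1 and GIP assays | Section 3.3 | Not stated |
| Stored-sample analyses | Section 3.3 | Not stated, open-ended |
| Database lock, blind settlement of exclusions | Not made a condition of release | – |

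For the 24th participant, values derived from the recordings and the compliance check cannot come before the trigger. For the other 23 participants the document does not say when processing is done. The close-out visit follows the trigger by the plan's own wording.

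**3. Which outcomes are exposed.** Total cholesterol is on the list run by the hospital clinical laboratory (Section 3.3), as are LDL cholesterol and triglycerides. Glucose, insulin and C-peptide from the glucose tolerance test go to the same laboratory. Section 2.4 adds per-subject verification of the primary endpoint. The measured values of these outcomes are little exposed. The exposed ones are those derived from recordings: heart rate variability, NIRS and the exercise test, and to a lesser degree ambulatory blood pressure, which is analysed in named software.

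**4. Does knowing the code inflate type I error through the choice of test?** Section 4.2 makes the paired t-test the default and adds: "If a variable is not normally distributed, a logarithmic transformation will be applied prior to statistical analysis, or non-parametric tests will be used". Null trials were simulated with n = 24. The normal case uses an SD of difference of 0.38. The lognormal case uses assumed log-scale SDs of 0.4 between and 0.3 within persons.

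- Smallest p-value of raw t, log t and Wilcoxon, chosen freely (10,000 trials): 6.2% normal, 6.5% lognormal. Another run of 10,000 gave 6.1% and 7.1%.
- The rule as written, with Shapiro-Wilk applied to the paired differences (an assumption), the t-test if passed, and the smaller of the log-t and Wilcoxon p-values if failed (10,000 trials): 5.1% and 5.0%.
- The same rule with normality judged on the measured values in each arm instead (20,000 trials): about 5% normal and about 6% lognormal.

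The Monte Carlo standard error is about 0.2 percentage points. For a cholesterol-like variable the gated rule stays near 5% on either reading.

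**The case against.** The strongest reply is that the document does not say any of this work will be late, or that those who do it will hold the code. The code goes to the principal investigator; nothing says it reaches the staff who process signals, run assays or do the statistics. Batching of assays and manual editing of artefacts are not mentioned either. Blinding during data collection might be meant to include deriving values from recordings. All this stands, and it limits the point to what the written rule permits. It does not remove the point, because the rule sets no barrier and the last participant's recordings exist only from the trigger visit onwards.

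A second reply is that blind sign-off of analysis choices belongs in a statistical analysis plan that is not shown. That also stands: such a plan, signed before the last visit, would settle transformations and multiplicity. It would not change the release event stated here.

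A third limit concerns exclusions. The document does not say whether someone who has completed both arms and is later found ineligible counts as discontinued. The reference to retrospective identification in Section 2.2.2 makes that reading possible, not certain.

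A reader might infer more: that every outcome is compromised, that the hormone assays are the main problem, or that type I error rises to about 6.5%. The documents do not support these readings. The primary measurement is made in the hospital laboratory. Glucagon, GLP-1 and GIP are not among the secondary outcomes named in Section 4.1. The 6.5% figure requires a free choice among three tests, which Section 4.2 does not grant.

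**Conclusion.** The point holds in a limited form. The protocol article states a release trigger that comes before steps which should be finished blind, and it makes neither completed signal processing nor settled exclusions nor a locked database a condition. The exposure is to operator-derived secondary outcomes and to late eligibility or compliance exclusions, the latter being the one route by which the primary comparison could be touched.

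The size of any bias cannot be derived from the document, and no effect on the primary result is shown. No type I error figure should be attached: the gated test rule stays near 5% when normality is judged on the paired differences, and the modest excess for skewed variables under the other reading depends on details the article does not fix. The conclusion assumes that the trigger is applied as written and that no other governing document delays release.

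**What to change.** Replace the trigger in Sections 2.1 and 2.3. The hospital pharmacy should release the code only when:

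- the planned outcome assays and the processing of heart rate variability, NIRS, exercise-test and ambulatory blood pressure data are complete;
- monitoring queries, including those from the close-out visit, and all exclusions have been settled blind;
- the database is locked.

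Extend the statement on assessor blinding from data collection to the same point. Exploratory assays run later on stored samples should use coded arm labels. The existing provision for immediate unblinding after a serious adverse event or pregnancy stays as it is.

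The cost is a short change of wording and a code release delayed until lock. Sample size, visits and measurements do not change. Once the code has been opened, blinding of this work cannot be restored, so the change has to be made before the last participant finishes.
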